### Statistical Analysis

To assess intervention efficacy, we will use repeated measure analysis of variance to detect differences in mean outcome scores between the 2 groups at T2 and at 2-month follow-up. All analyses will be conducted in accordance with the intention-to-treat principle. Missing data will be imputed using Markov Chain Monte Carlo [74]. Results will be expressed as differences in mean scores between the 2 groups with 95% confidence intervals. *P* values<.05 will be considered statistically significant.

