**Methods:**

This will be a multicenter, multi-informant, and multimethod randomized controlled trial. Participants will be adolescents (N=80), aged 10 to 18 years, with clinical levels of posttraumatic symptoms, who are randomized to receive either the Muse therapy sessions and treatment as usual (intervention) or treatment as usual alone (control). Data will be collected at 3 measurement instances: pretest (T1), posttest (T2), and at 2-month follow-up. Primary outcomes will be posttraumatic symptoms (self-report and mentor report) and stress (self-report) at posttest. Secondary outcomes will be neurobiological stress parameters under both resting and acute stress conditions, and anxiety, depression, and aggression at posttest. Secondary outcomes also include all measures at 2-month follow-up: posttraumatic symptoms, stress, anxiety, depression aggression, and neurobiological resting parameters.

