### Objectives

The primary aim of this study is to investigate the effectiveness of Muse as an addition to treatment as usual in reducing posttraumatic symptoms (self- and mentor report) and stress (self-report) compared with treatment as usual in traumatized adolescents in residential care. We expect that playing Muse will result in a greater reduction of posttraumatic symptoms and stress than treatment as usual alone.

As a secondary aim, we will investigate the effectiveness of Muse on neurobiological stress systems under both resting and social stress conditions. It is hypothesized that participants who play Muse will show normalized neurobiological parameter compared to participants in the control group. We will also assess the effects of playing Muse on anxiety (self-report), depression (self-report) and aggression (self- and mentor report). It was expected that playing Muse would result in reduced anxiety, depression, and aggression.

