### Measures

#### Questionnaires

The screening instrument is the CRIES-13 [49], a questionnaire with 13 four-point items to screen whether adolescents suffer from posttraumatic symptoms.

Posttraumatic symptoms will be measured by participants’ self-report as well as by mentor report. The Child Report of Posttraumatic Symptoms (CROPS) [60] is a self-report questionnaire that consists of 24 three-point items. The Parent Report of Posttraumatic Symptoms (PROPS) [60] is a 30-item questionnaire that measures posttraumatic symptoms as reported by parents or other caretakers. In this study, participants’ group home mentors will fill out the questionnaire. Several studies have demonstrated the validity and reliability of the CROPS and the PROPS in general populations [61]. Additionally, the CROPS has been validated in a sample of juvenile offenders [62]. The CROPS and the PROPS have been jointly developed so that the CROPS focuses on internal thoughts and feelings, whereas the PROPS focuses on observable behaviors.

Stress will be examined with the 7-item stress subscale of the Depression Anxiety Stress Scales (DASS-21) [63,64]. The DASS-21 is a self-report questionnaire that in total consists of 21 four-point items. Its validity and reliability are good and the subscales have an excellent internal consistency [63].

Anxiety will be measured with the 7-item anxiety subscale of the DASS-21 [63,64].

Depression will be measured with the 7-item depression subscale of the DASS-21 [63,64].

Aggression will be measured by participants self-report as well as by mentor report. The Reactive and Proactive Aggression Questionnaire (RPQ) [65] is a self-report questionnaire that is composed of 23 three-point items. The RPQ consists of proactive aggression and reactive aggression subscales. Its validity and reliability are good, and both subscales have good internal consistency [65]. The Parent-rating scale for Reactive and Proactive Aggression (PRPA) [66] is a questionnaire that can be filled out by parents or other caretakers. The PRPA has 11 three-point items and consists of reactive aggression and proactive aggression subscales. The PRPA total score and both its subscale scores have good validity [66].

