### Sample Size Calculation

Power calculations were performed using G*Power [72]. An a priori power analysis for analysis of variance (repeated measures, within-between interaction) was conducted. Based on previous meditation-based interventions for posttraumatic stress [32,34-36,73], we expected a small to medium effect size of *d*=0.30 and a repeated measures correlation of 0.60. To achieve a statistical power of at least .80, a sample size of 72 participants was required. We aim to include 80 participants in total to allow for 10% attrition, which was estimated from previous studies [44,45,47] on game-based interventions in this population.

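### Three unranked primary outcomes share a flat .05 threshold with no stated success rule, so the 5% error rate is not secured for the primary conclusion

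*Protocol article*

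**What the plan says.** The abstract (Methods) states: "Primary outcomes will be posttraumatic symptoms (self-report and mentor report) and stress (self-report) at posttest". The Objectives repeat the same three, with the aim of "reducing posttraumatic symptoms (self- and mentor report) and stress (self-report) compared with treatment as usual". Neither place ranks them.

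Under Measures, Questionnaires, the two views of posttraumatic symptoms stay separate: "Posttraumatic symptoms will be measured by participants’ self-report as well as by mentor report". The instruments are CROPS and PROPS, and no composite is defined. Stress is the 7-item DASS-21 subscale.

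The Statistical Analysis section gives the method ("we will use repeated measure analysis of variance to detect differences in mean outcome scores between the 2 groups"), the form of reporting ("Results will be expressed as differences in mean scores between the 2 groups with 95% confidence intervals") and the threshold: P "values<.05 will be considered statistically significant". It says nothing specific to the primary family.

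The Sample Size Calculation is for one within-between interaction test and names no outcome. Its inputs are given as "we expected a small to medium effect size of *d*=0.30 and a repeated measures correlation of 0.60", and from these it derives a need for 72 adolescents at 80% power.

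**The concern.** The abstract's Conclusions section promises a single answer on whether the therapy improves posttraumatic stress. Three tests feed that answer, and nothing says how to combine them if they disagree.

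Disagreement is foreseeable. The Questionnaires section explains that CROPS covers inner thoughts and feelings while PROPS covers observable behaviour, and the two come from different informants.

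If the authors, or a reader, take one significant result out of three as success, the 5% level applies to each test but not to the conclusion. If all three are required, there is no inflation, but power for the conclusion is below the planned 80%. The article leaves both readings available after the data are seen.

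**Working it through.** **Inputs from the protocol article**
- Three primary outcomes at T2 (abstract; Objectives).
- Threshold .05 per test (Statistical Analysis).
- d = 0.30, repeated-measures correlation 0.60, power .80, N = 72, raised to 80 for 10% attrition (Sample Size Calculation).

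**Assumptions**
- Two-sided tests. The article does not say so, but the F test has no direction and 95% intervals are reported.
- Correlations between the three outcomes. The document gives none; its 0.60 is between time points.

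**Step 1: reproduce the planned sample size.** For the interaction, with f = d/2 = 0.15 and m = 2 time points:

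λ = f² × N × m / (1 − ρ) = 0.0225 × 72 × 2 / 0.40 = 8.1, with 1 and 70 degrees of freedom.

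At α = .05 the noncentral F power is 0.801, and 72 / 0.90 = 80. The plan's figures reproduce, and they rest on one test at an unadjusted .05. With m = 3 the required N would be 60.

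**Step 2: family-wise error if any one of three counts as success.**

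Independent outcomes, two-sided: 1 − 0.95³ = 0.143. Errors favouring Muse only: 1 − 0.975³ = 0.073, against 0.025 for one test.

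For a common correlation r between the test statistics:

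1 − ∫ [Φ((1.96 − √r·u)/√(1−r)) − Φ((−1.96 − √r·u)/√(1−r))]³ φ(u) du

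The second Φ term is dropped for errors in one direction.

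| Assumed r | Either direction | Favouring Muse only |
|---|---|---|
| 0 | 14.3% | 7.3% |
| 0.3 | 13.6% | 6.8% |
| 0.5 | 12.5% | 6.3% |
| 0.7 | 10.9% | 5.5% |
| 0.8 | 9.8% | 4.9% |
| 0.9 | 8.4% | 4.2% |
| Single test | 5.0% | 2.5% |

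Simulation with 3 million draws agrees. With unequal correlations (0.5 to 0.7 for the two self-reports, 0.1 to 0.3 across informants) the two-sided figure is 12.7% to 13.6%.

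**Step 3: cost of control.** At .05/3 = .0167 and λ = 8.1, power is 0.653 at N = 72. At N = 80 it is 0.709. Reaching 80% at .0167 needs 96 completers, or 96 / 0.90 = 107 enrolled.

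These figures depend on how d = 0.30 is read. For a difference in change δ, in SD units of the outcome, the same test has λ = δ² × N / (4 × 2(1 − ρ)) = δ² × 72 / 3.2 = 22.5δ². Setting this to 8.1 gives δ = 0.60, so the stated N corresponds to a 0.60 SD difference in change. If 0.30 is itself the difference in change, λ = 22.5 × 0.09 = 2.03. Power at N = 72 is then about 29% at .05 and 16% at .0167.

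**Step 4: cost of requiring all three.** No error inflation arises. If each test has power 0.801 and the outcomes are independent, the power to win on all three is 0.801³ = 0.51. It is higher when they are positively correlated.

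**The case against.** **The article states a threshold, not a success rule.** This stands. A reader might infer that the plan allows success on any one outcome. No sentence says so. The expectation in the Objectives joins posttraumatic symptoms and stress, which is closer to requiring all of them, and under that rule there is no inflation. What the text supports is narrower: the rule is unstated and the any-one reading is not excluded.

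**Multiplicity is often left to a full protocol or analysis plan, and an adjusted P could also be compared with .05.** This stands in part. An unseen document may contain an adjustment. But the article does state a decision threshold over three co-equal primaries. It is therefore fair to say that the rule as published does not hold the primary family at 5%.

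**The range 11% to 14% overstates the risk of a false claim of benefit.** This stands. That range counts errors in both directions and assumes correlations between 0 and 0.7. Errors favouring Muse are about half as frequent, and stronger correlation lowers both columns. A claim confined to posttraumatic symptoms would rest on two tests: 1 − 0.95² = 9.75% if independent. All of these still exceed their nominal level.

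**The same threshold also covers a long list of secondary and follow-up measures.** A reader might conclude that significance language must be dropped there. The document does not support that as an error. It labels these outcomes secondary and commits to mean differences with 95% intervals; going further is a reporting preference.

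**Conclusion.** The concern holds in a limited form. Three unranked primary outcomes are paired with a flat .05 and no success rule, order or adjustment. On the any-one reading, the two-sided family-wise error runs from about 14% (independent) through 11% (r = 0.7) to 8% (r = 0.9). In the direction favouring Muse it is 7.3%, 5.5% and 4.2%, against 2.5%.

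The figures rest on two-sided tests and assumed correlations, and they apply only if one success is treated as enough. They are not the error rate of a rule the article has adopted.

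This should be fixed, but it does not undermine the trial: the primaries are few, prespecified and separate from the secondaries.

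**What to change.** State in the Statistical Analysis section, before outcomes are compared, one rule for the three primary T2 tests. If the full protocol or analysis plan already contains one, report it there. Any of these would do:

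- **Fixed sequence**, for example CROPS, then PROPS, then DASS-21 stress, each at .05, stopping at the first non-significant result. The first test keeps its planned power. The cost is that later outcomes may never be formally tested.
- **Holm** across the three. At the strictest step (.0167) with N = 72, power falls from about 80% to about 65% on the reading that reproduces the planned N, and further if d = 0.30 is the difference in change.
- **All three must be significant**, each at .05. This removes the inflation without adjustment, at the cost in power shown in Step 4.

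The change is one or two sentences and needs no new data. The Sample Size Calculation should then say which outcome, and which effect on it, the 72 refers to. Secondary outcome reporting need not change.

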### Ethical and Safety Issues

Ethical review and approval of this study has been provided by the medical-ethical committee Arnhem-Nijmegen (protocol NL58674.091.16). All substantial amendments will be presented to the committee and competent authority. Before participants are included in the study, they will be informed about the study design, including randomization. Participants who are assigned to the control group will be offered the opportunity to play Muse after the study has ended. Participants can withdraw from participation at any time without consequences.

Participant privacy will be protected by allocating identification numbers to personal information that is traceable in a separate file using double-key encryption. Data will be analyzed in a way that no conclusions can be drawn about individual participants. The 3 researchers that will have access to the data work at the residential institutions where the study is being conducted. Data entry will be double-checked to ensure accuracy. Biological materials will be stored in a locked cabinet or a locked medical freezer at Pluryn until the end of the study. The material will be destroyed after laboratory analysis, as requested by the medical-ethical committee that approved the study.

Adverse events reported by participants or group care workers or observed by the researchers will be recorded and assessed in collaboration with participant’s clinician. The potential relation to the intervention will be examined and participants will be followed until they are reached stable. The risk in participating for this study is considered negligible, but if a participant seems negatively affected by the measurements or intervention, study participation will be discussed with the clinician and discontinued, if necessary.

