### Interventions

All participants receive treatment as usual: the treatment as recommended by their clinicians regardless of this study (eg, individual or family therapy; medication). There are no restrictions for the type of interventions that participants can receive other than trauma-focused treatment, we only keep track of them. Participants in the intervention group will receive the intervention sessions as an addition to treatment as usual.

Muse is a game-based meditation app that is played on an iPad with a electroencephalography (EEG)–based headband that utilizes real-time neurofeedback. The intervention takes 6 weeks and consists of two 15- to 20-minute gameplay sessions per week. If participants are unable to make it to a session, this session will be rescheduled. All participants will complete 12 gameplay sessions in total. These sessions will take place in an office room located on the campus of the residential institution. Muse includes 10 relaxation tutorials that resemble elements of trauma-focused cognitive behavioral therapy such as deep-breathing techniques [42]. The tutorials are followed by 3-minute meditation sessions. The meditation tutorials are in English, so we have created a standardized protocol with Dutch translations of each tutorial. The gameplay sessions will be supervised by research assistants who are trained to explain the tutorials according to this protocol.

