**After**							
	0 minutes	Recovery		ANS recovery		Post	
	10 minutes	—		—		+10	
	20 minutes	—		—		+20	
	40 minutes	—		—		+40	

^a^ANS: autonomic nervous system.

The posttest (T2) will take place in week 8 and includes, like the pretest (T1), an interview, aquatic video, social stress task, and a hair cortisol measurement. Since participants will be exposed to the social stress task twice, it is expected that they show habituation-related decreased levels of stress at T2 [58,59]. To lower the risk for stress habituation and to improve methodological rigor for the second social stress task, participants will be given another story introduction that is comparable to the story that will be used for T1. At the end of T2, participants will be debriefed and told that the video recordings were deleted immediately after the measurement session.

The 2-month follow-up will take place in week 16 and includes an interview, aquatic video, and a hair cortisol measurement. The 2-month follow-up measurement is conducted to provide additional information about potential long-term intervention effects. Therefore, we will use questionnaires and the parameters to measure neurobiological activity during rest that are relatively simple to obtain (ie, a 5-minute autonomic nervous system measurement during the aquatic video and cutting the hair). Measuring neurobiological reactivity requires the execution of a stress task that is time-consuming, and even more important, eliciting stress among traumatized adolescents is not without risks and should only be done when essential for research purposes. For those reasons, neurobiological reactivity to acute stress was not included at 2-month follow-up measurement.

Participants will receive a gift voucher of €15 (approximately US $17.86) at T1, a gift voucher of €10 (approximately US $11.91) and a stress ball at T2, and a gift voucher of €15 at 2-month follow-up measurement. Participants’ mentors (ie, the group home worker with whom they have the most contact) will fill in the questionnaires in the same week as when the measurements with the participants are conducted.

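### Adverse events are picked up partly by researcher observation, which is far more frequent in the Muse arm, so any count by arm is at risk of ascertainment bias

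*Protocol article*

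**What the plan says.** Ethical and Safety Issues names three sources of adverse events: participants, group care workers and researchers. "Adverse events reported by participants or group care workers or observed by the researchers will be recorded", and events are then assessed with the participant's clinician. On causality it says: "The potential relation to the intervention will be examined". It adds that "if a participant seems negatively affected by the measurements or intervention, study participation will be discussed with the clinician and discontinued, if necessary". No scheduled enquiry about adverse events is described.

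Under Interventions, the Muse arm receives two sessions a week for six weeks, and "The gameplay sessions will be supervised by research assistants". Study Design gives both arms three measurement occasions: T1, T2 and the 2-month follow-up. Allocation and Randomization says that group assignment is not masked. Study Setting describes 24-hour care in group homes for all participants.

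Two statements bear on the level of risk. Study Procedure, explaining why the stress task is left out at follow-up, says that "eliciting stress among traumatized adolescents is not without risks and should only be done when essential for research purposes". Ethical and Safety Issues says: "The risk in participating for this study is considered negligible".

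**The concern.** One of the three stated sources, observation by researchers, is open to the two arms to very different degrees. While the intervention runs, study staff are scheduled to see Muse participants twice a week and controls not at all. Those sessions also give Muse participants extra occasions to mention an event to study staff. If recorded events are later reported by arm, an excess under Muse could reflect closer observation, harm, or both, and the records would not separate them.

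The stated causality question fits the control arm poorly. Controls do not receive Muse until the study has ended, so their study-specific exposure is the measurements, including the stress task at T1 and T2. The article recognises that measurements may affect a participant badly, but it does not say that an event's relation to them will be recorded.

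**Working it through.** **Scheduled contacts with study staff**

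Inputs: 6 weeks and 2 sessions per week (Interventions); 3 measurement occasions in both arms (Study Design); intervention in weeks 2-7 (Table 1).

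- Muse sessions: 6 × 2 = 12, which agrees with the total stated under Interventions.

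| Period | Muse | Control | Ratio |
|---|---|---|---|
| T1 to follow-up | 12 + 3 = 15 | 3 | 5.0 |
| After T1 | 12 + 2 = 14 | 2 | 7.0 |
| Weeks 2-7 | 12 | 0 | not defined |

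The row after T1 is the relevant one, because it covers the time when the arms differ. These are scheduled contacts only. The recruitment and assent meetings come before T1 in both arms and are not counted.

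**What the imbalance could do to counts**

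The document gives no detection rates, so this is an illustration under assumptions. Let the true event rate be equal in the two arms. Let *g* be the probability that an event is recorded through the channels that both arms share (care workers, self-report). Let *q* be the probability that any one scheduled contact after T1 picks it up, independently of the others. Then

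- P(recorded | Muse) = 1 − (1 − g)(1 − q)^14
- P(recorded | control) = 1 − (1 − g)(1 − q)^2

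Example with g = 0.6 and q = 0.05:

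- Muse: 1 − 0.4 × 0.95^14 = 0.805
- Control: 1 − 0.4 × 0.95^2 = 0.639
- Ratio: 0.805 / 0.639 = 1.26

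Ratio of recorded events, Muse to control:

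| g | q = 0.02 | q = 0.05 | q = 0.10 |
|---|---|---|---|
| 0 | 6.22 | 5.25 | 4.06 |
| 0.3 | 1.44 | 1.79 | 1.94 |
| 0.6 | 1.13 | 1.26 | 1.34 |
| 0.9 | 1.02 | 1.05 | 1.06 |
| 1 | 1.00 | 1.00 | 1.00 |

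In this model the ratio is above 1 whenever the shared channels miss anything. Its size depends almost wholly on *g*, which the document does not give.

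**Causality wording**

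Set side by side, the paragraph in Ethical and Safety Issues accepts two possible sources of harm, measurements and intervention, when it deals with continued participation. It names one, the intervention, when it deals with relation.

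**The case against.** **No harm comparison is planned.** Adverse events are not among the outcomes in the Abstract, and Statistical Analysis covers efficacy only. Events are handled one participant at a time. This stands. A reader might infer that a planned harm comparison is biased, but the document contains no such comparison. The point applies to any tabulation by arm that is made later.

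**The arms share a strong detection channel.** Group care workers look after all participants around the clock, and mentors complete forms at each measurement in both arms. This also stands, and it is why the bias may be small. It does not remove the imbalance. Mentors are group home workers who know the allocation, and the Discussion accepts that differential expectations might bias outcomes. The same could hold for the reporting of events.

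**Controls may be seen informally.** The researchers with data access work at the institutions, and the article does not say whether the researchers who observe events include the session assistants. This is fair, so the counts above describe scheduled contact only. Nor does the article say that participant reports are unprompted, only that no enquiry is described.

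**Stress-task harm is recognised.** A reader might infer that such harm goes unattributed or is filed as unrelated. The document does not support that: events are assessed with the clinician, and harm from measurements is named. The task is also scheduled alike in both arms, so it does not by itself bias a contrast between them. What remains is that relation to the measurements is not stated.

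**The risk statements can coexist, and detail may sit in the full protocol.** A low but nonzero risk fits both statements, so this part is a matter of wording. Prompts and causality categories may well be in the unseen full protocol, and their absence here is not the point. The unequal observation channel and the causality sentence are in the article itself.

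**Conclusion.** The point holds in limited form. By the article's own rules, researcher observation is unmasked and unequal: 14 scheduled contacts after T1 against 2. Any adverse event count by arm is therefore at risk of ascertainment bias towards more recorded events under Muse. The contact counts follow directly from the document. The effect on event counts does not: with equal true rates and *q* between 0.02 and 0.10, the ratio is 1.4-1.9 if shared channels catch 30% of events, 1.1-1.3 at 60%, and 1.02-1.06 at 90%. The article does not establish that an event is far more likely to be recorded under Muse. No stated figure is wrong and no planned analysis is affected. The causality wording and the two risk statements are lesser matters of clarity.

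**What to change.** - At T2 and week 16, ask every participant (in the existing interview) and every mentor (with the existing questionnaires) the same fixed adverse event question, covering the period since the last measurement.
- Base any tabulation by arm on that source alone. List events observed in Muse sessions separately.
- In both arms, record relation to the intervention and relation to the study measurements as two separate fields.
- Reconcile the risk wording in Ethical and Safety Issues with that in Study Procedure.

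**Cost.** One added question at contacts already scheduled, one extra field, and a few more minor events recorded. Enrolment began in January 2018, so participants already past those visits would not be covered, and any report should say so. The fix makes the opportunity to report equal. It does not mask participants or mentors, so some reporting bias could remain.

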### Recruitment

At adolescents’ admission to the residential institutions taking part in the study, the CRIES-13 is included in the standard questionnaire battery that adolescents fill out at intake. Adolescents with a clinical score of posttraumatic symptoms on the CRIES-13 (≥30), filled in less than 3 months before T1, will be considered eligible participants for this study. We will include adolescents with clinical levels of posttraumatic symptoms rather than adolescents who qualify for the diagnosis of posttraumatic stress disorder because many adolescents who do not meet the criteria for posttraumatic stress disorder do suffer from posttraumatic symptoms and are in need of treatment [50].

Additionally, clinicians will be asked whether the adolescent in question can be invited to take part in this study. After clinician consult, eligible participants will be contacted by the coordinating researcher who will explain the studies. We will obtain verbal and written assent from all participants, and when they are younger than the age of 16, also written consent from their legal guardians. Potential participants will be invited for an individual meeting with the coordinating researcher who will explain the study. Participants will be explicitly informed about the study design and that they can quit study participation at any moment without disadvantages. The researcher will also bring information letters with information on all aspects of the study. When adolescents initially agree to participate, they will be given the information letters, and 2 to 3 weeks later, they will be asked for their written assent and invited for the pretest measurement (T1).

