### Allocation and Randomization

If all inclusion and no exclusion criteria are fulfilled, participants will be randomly assigned (1:1 ratio) to 1 of the 2 groups using a randomization schedule that is generated by a Python script and stratified by gender, intellect, and residential institution. Allocation to groups is not masked, but participants and their mentors will not be informed about the specific expectations regarding posttraumatic symptoms and neurobiological stress reactivity. We will explain that Muse is a relaxation app, designed to help participants deal with stress. Participant enrollment and assignment to the groups will be performed by the first author.

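### The response to apparent harm is to stop study participation as a whole; stopping only Muse or the stress task would keep the outcome scores (minor, cheap to improve)

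*Protocol article*

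**What the plan says.** The article's Ethical and Safety Issues section gives one response to apparent harm: "if a participant seems negatively affected by the measurements or intervention, study participation will be discussed with the clinician and discontinued, if necessary". The same section provides for adverse events: "The potential relation to the intervention will be examined and participants will be followed until they are reached stable". It calls the risk of taking part negligible.

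Recruitment uses the same term for leaving the study altogether: adolescents are told that "they can quit study participation at any moment without disadvantages".

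On who is exposed to what:

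- Interventions: "Participants in the intervention group will receive the intervention sessions as an addition to treatment as usual".
- Ethical and Safety Issues: "Participants who are assigned to the control group will be offered the opportunity to play Muse after the study has ended".
- Allocation and Randomization: "Allocation to groups is not masked".
- Study Procedure: both arms do the social stress task at T1 and T2. It is left out at follow-up because "eliciting stress among traumatized adolescents is not without risks and should only be done when essential for research purposes", while the questionnaires are kept.

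Statistical Analysis promises an intention-to-treat analysis and states: "Missing data will be imputed using Markov Chain Monte Carlo".

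**The concern.** The rule acts on participation in the study, not on the component that seems to cause the harm. Read naturally, a participant who reacts badly to Muse or to the stress task loses the T2 and week 16 assessments as well. Nothing in the article provides for stopping one component and keeping the scores. Interventions only reschedules missed sessions and expects all 12 to be completed.

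Participants stopped under this rule are selected because they appear to be worse. That is the state measured by the primary outcomes: the CROPS, the PROPS and the stress subscale of the DASS-21. Since only the Muse arm can be affected by Muse during the study, such losses could be more frequent there. Imputation keeps these participants in the analysis, but it does not fully recover worsening that the observed data do not predict. The T2 and follow-up differences would then look somewhat better for Muse than they are.

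The authors apply the relevant principle elsewhere. They defend exclusion on clinician advice because it precedes randomisation and so affects both groups equally. A clinician-led stop after randomisation does not have that protection.

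**Working it through.** **Inputs from the article.** Sample Size Calculation: d=0.30, correlation 0.60, power 0.80, N=72, raised to 80 for 10% attrition. Allocation is 1:1, so 40 per arm. Significance level 0.05. The article gives no rate of stopping for harm, so the losses and the worsening below are assumptions.

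**1. The plan's own figure.** For the within-between interaction, λ = f²·N·m/(1−ρ), with f = d/2 = 0.15, m = 2 measurements and ρ = 0.60. At N=72, λ = 0.0225 × 72 × 2 / 0.40 = 8.1, which gives power 0.801. Then 72/0.90 = 80. Both figures reproduce. (With m = 3 the required N would be 60.)

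**2. The contrast behind N=72.** The variance of a change score is 2 × (1 − 0.60) = 0.80. At 36 per arm, SE = √(0.80 × 2/36) = 0.211. Setting (δ/SE)² = 8.1 gives δ = 2.846 × 0.211 = 0.60 SD. So 72 participants give 80% power for a between-arm difference in change of 0.60 SD, not 0.30 SD. The bias is therefore set against both figures.

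**3. Standard error at 40 per arm.** Change score: √(0.80 × 2/40) = 0.200. Baseline-adjusted: √(2/40 × (1 − 0.36)) = 0.179. T2 only: √(2/40) = 0.224.

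**4. Bias.** Bias = (Muse losses − control losses)/40 × worsening not predicted by the observed data. The worsening is set at 1.0 SD for every loss. The last column is the chance, with no true effect, of a significant result favouring Muse (nominally 2.5%), from the normal approximation with SE 0.200.

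| Muse / control losses | Bias (SD) | In SE (0.200) | Share of 0.30 | Share of 0.60 | Error favouring Muse |
|---|---|---|---|---|---|
| 1 / 0 | 0.025 | 0.12 | 8% | 4% | 3.3% |
| 4 / 2 | 0.05 | 0.25 | 17% | 8% | 4.4% |
| 4 / 0 | 0.10 | 0.50 | 33% | 17% | 7.2% |
| 4 / 4 | 0 | 0 | 0% | 0% | 2.5% |

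Across the three standard errors, 0.10 SD is 0.45 to 0.56 SE. The 4 / 0 row is an upper corner. It uses one arm's whole attrition allowance (10% of 80 = 8, about 4 per arm) with no control losses. Each loss must also be 1.0/0.80 = 1.25 residual SDs worse than imputed, since the residual SD is √(1 − 0.36) = 0.80.

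**5. Power.** For the 0.60 SD contrast, losing 1 or 4 of the 40 Muse participants and no controls lowers power from 0.842 to 0.837 or 0.822. The issue is possible bias, not sample size.

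**The case against.** The strongest case against is that this is a condensed safety sentence about protecting participants. It does not say that questionnaires cease, and it does not forbid a lesser step. The step is discretionary, and the ethics-approved protocol, which is not shown, may separate stopping Muse from leaving the study. The one component that the article itself calls risky is the stress task, which both arms undergo. Nothing suggests that supervised relaxation sessions of 15 to 20 minutes make adolescents worse. In any trial of an add-on treatment, only the treated arm can react to it. The loss rates are assumed, and the proposed wording still leaves the clinician free to stop everything.

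Much of this stands. It makes the point minor and the size unknown. It does not remove the point, because the article states a rule and names what is stopped. This is more than detail left to a fuller document. The study's own handling of the stress task at follow-up shows that burden can be separated by component, and the harm rule does not carry that over.

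A reader might infer that the article requires all data collection to end after harm, or that harm from Muse would be hidden. The text supports neither. The end of outcome collection is the natural reading, not an explicit statement, and adverse events are recorded, examined for a relation to the intervention and followed until stable. That follow-up is not described as collecting outcome scores, however.

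**Conclusion.** The point holds as a cheap improvement of minor severity. On its natural reading, the rule gives up the T2 and follow-up scores of participants chosen for apparent worsening, and one of its two triggers exists only in the unmasked Muse arm. The bias would favour Muse, and it is zero if losses and worsening are equal in the two arms.

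Its size is unknown and probably small: 0.025 SD for each net extra Muse loss that is 1.0 SD worse than imputed. A reader might infer a serious threat by setting the 0.10 SD corner against d=0.30, where it looks like a third of the effect. The documents do not support that. Nothing in them points to such a loss pattern, and against the 0.60 SD contrast that N=72 is powered for, the corner is about 17% and a single loss about 4%.

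**What to change.** In Ethical and Safety Issues, state that:

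- the clinician may stop the Muse sessions or the stress task alone, and this does not by itself end outcome collection;
- the mentor forms (PROPS, PRPA) continue at weeks 8 and 16, and so do the self-report questionnaires (CROPS, DASS-21, RPQ), unless assent or consent is withdrawn or the clinician judges them unsuitable;
- the component stopped is recorded by arm and reason;
- full discontinuation remains available to the clinician.

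The mentor forms keep one primary outcome, the PROPS, without any contact with the adolescent.

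Cost: two or three sentences with matching consent wording. Enrolment began in January 2018, so this is an amendment that may have to go to the committee, and renewed assent or guardian consent may be needed. The few participants affected would face interviews of about 30 minutes, which is a real burden for adolescents already judged to be negatively affected and the reason for the clinician's exemption. No extra participants or procedures are needed.
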